#### Nicotine dependence and urge to smoke (baseline, one, three and six months)

The heavy smoking index will be used to assess nicotine dependence from smoked tobacco.^49^ The Mood and Physical Symptoms Scale (MPSS)^50^ will also be administered. The scale assesses withdrawal symptoms including anxiety, depression, irritability, restlessness, hunger, concentration and sleep.

#### Quitting smoking intentions, motivations and behaviors (baseline, one, three and six months)

The four item motivation to quit (MTQ) questionnaire^33^ will be used to measure motivation to quit smoking. It is scored by summing the responses to each item. The scores range from 4 to 19 where a higher score indicates greater motivation to quit. Questions from the Global Adult Tobacco Survey (GATS)^48^ will also be used to assess smoking cessation intentions, motivations and behaviours.

#### Mediators of smoking cessation (baseline, three and six months)

A set of questions related to the interventions’ behaviour change targets will be developed during the intervention adaptation phase and used to assess the mediators of smoking cessation in this study.

#### Quality of life (baseline, three and six months)

The EQ-5D-5L^51,52^ will be used to measure health-related quality of life (HRQoL). EQ-5D is a standardised measure of health status developed by the EuroQol Group in order to provide a simple, generic measure of health for clinical and economic appraisal, where health is characterised on five dimensions (mobility, self-care, ability to undertake usual activities, pain/discomfort, anxiety/ depression).

#### Health services use (baseline, three and six months)

Participant use of health services and other smoking cessation services outside the study will be assessed. A health service utilisation questionnaire previously used in some of our studies such as the MCLASS trials^53^ or the Client Service Receipt Inventory, adapted to the context of Pakistan and India,, will be used to collect number and type of contacts with doctors, hospital admissions, pharmacy visits and medication prescriptions for all participants. Information on contact with traditional healers will also be recorded.

#### Mental and physical health (baseline, three and six months)

PHQ-9^54^ will be used to measure depressive symptoms. This nine item questionnaire is scored from 0 to 27, and a higher score indicates more severe depressive symptoms. The GAD-7^55^ will be used for measuring anxiety. This seven-item instrument is scored from 0 to 21, with a higher score indicating more severe anxiety. The SF-12 which consists of two subscales: a physical health component and a mental health component will also be administered. Both components are scored from 0 to 100, with 0 indicating the lowest level of health and 100 the highest level of health measured by the scale.^56^

#### Physical body measurements (baseline, three and six months)

Physical body measurements will include height and weight which will be measured by trained personnel according to the WHO protocols.^57^ These will be used to determine the body mass index. Physical body measurements of the trial participants will not be measured if the recruitment and assessments are conducted remotely, or the intervention is done delivered remotely.

#### Smoking cessation pharmacotherapy adherence (one and three months)

For the IMPACT 4S group, self-reported medication adherence to smoking cessation pharmacotherapies will be assessed retrospectively based on a 4-day recall.^58^

An adherence index will be calculated by the formula:

Total number of doses taken X 100

Total number of doses prescribed

Participants with more than 80% of adherence will be considered as having high adherence and those with less than 80% will be considered as having low adherence.^59^ Participants who report missed doses will be asked to provide reasons for missing their medications.

- - 1. Participants’ preference between face-to-face and remote delivery of intervention for those who are on the IMPACT 4S intervention arm (at baseline)

Participants will be asked to indicate their preferred mode of intervention delivery (face-to-face or remote), and the reasons for their preference.

- - 1. Carers/ family members involvement (at baseline)

Participants will be asked to indicate whether they had been accompanied by a carer or family member at any of the intervention session, and whether they received help with any of the intervention activities from a carer/ family member.

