Participants in this arm will also be offered pharmacological support to aid smoking cessation (nicotine replacement therapy or bupropion either separately or ideally in combination). Pharmacotherapies will be provided for a minimum period of three months. Participants who opt to take bupropion will be referred to their medical doctor for assessing suitability of prescribing bupropion. Participants will be offered sustained-release bupropion, 150 mg/d for the first week and 300 mg/d thereafter. The pharmacological support will be provided for free within the trial. The participants will be scheduled for prescribed medication collection during their face-to-face sessions. In case of changes in mobility restrictions as complying to the local government guideline for managing the upcoming Covid-19 pandemic situation, all scheduled prescribed medication shall be dispatched or personally delivered to the participants’ residential address by post or by research assistants, respectively. Medications for one month will be handed over to them personally by the research staff. An excel sheet log will be maintained for the dispensation, consumption, replenishing and monitoring of Bupropion/Nicotine gums for all the participants who choose pharmacotherapy. The excel sheet log will be filled for medication related details by the research assistants delivering the 4S intervention to the participants and will be centrally managed by the trial manager. The trial manager and the research assistant will monitor the excel sheet log daily to verify if patients would be close to finishing their one-month’s stock of Bupropion/Nicotine gums and need replenishment of a fresh stock. Patient participants who are close to finishing their medications will be given a telephone call one week in advance and asked to visit the NIMHANS campus again to collect the smoking cessation medication for another month; in case, they cannot come to collect the medications, the medications will be personally delivered to the patients. The medications will be provided for a period of three months in total. If there is requirement of bupropion/nicotine gums beyond three months, they will be referred to the treating clinical unit. The patients will be reimbursed the travel costs and compensated for the time they spent in procuring the medication from NIMHANS. The patients will be educated about the correct dosage and method of use, side effects of bupropion/nicotine gums along with an information leaflet on the medications and will be provided contact details to report side effects and for advice. A referral to emergency services will be facilitated in case of a serious adverse event. The participants will be informed to keep the medications in their safe custody and out of reach of children. bupropion/nicotine gums are medications that are routinely prescribed for smoking cessation, including for persons with severe mental illness. Suicide risk assessment will be carried out during the sessions in the intervention arm. Consent to contact family members in case the patient is not reachable on telephone will be sought to mitigate any risks associated with overdose. In case of overdose, a referral to the nearest emergency services will be facilitated. The adherence to medications will be documented in the counsellor’s record book in each session.

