**Table 1. Baseline and follow-up measurement**

| **Measurement** | **Baseline** | **1 month**  **(Follow-up 1)** | **3 months**  **(Follow-up 2)** | **6 months**  **(Follow-up 3)** |
| --- | --- | --- | --- | --- |
| Demographic data | X |  |  |  |
| Preference for mode of intervention delivery | X |  |  |  |
| Carers/ family members’ involvement | X |  |  |  |
| Details of psychiatric medication | X | X | X | X |
| Smoking status | X | X | X | X |
| Nicotine dependence and urge to smoke | X | X | X | X |
| Quitting smoking intentions, motivations and behaviours | X | X | X | X |
| Mediators of smoking cessation | X |  | X | X |
| Health-related quality of life | X |  | X | X |
| Mental and physical health | X |  | X | X |
| Health services use | X |  | X | X |
| Physical body measurements (height; weight) | X |  | X | X |
| Smoking cessation pharmacotherapy adherence |  | X | X | X |
| Process evaluation questionnaire and interviews |  |  | X |  |

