### Analysis of economic and quality of life data

The completeness of returned HRQoL and health care utilisation data will be assessed to inform an economic evaluation alongside a full RCT. Returned service use data will be used to revise questionnaires used in a full trial.

Costs of delivering the interventions will be measured by recording the resources utilised in the delivery of the IMPACT 4S intervention (including behavioural support, CO monitoring and feedback, pharmacotherapy, costs for telephone/remote modes, client information-sheets, advisor’s resource for clients’ records and information leaflet costs) and BA (including the counselling and information leaflet). We will also capture the costs of intervention setup, training, as well as ongoing support and supervision of the personnel delivering the intervention. We will capture participant travel costs and travel time to attend intervention sessions, including whether they were accompanied by carers/families, and the related travel and time costs. For each trial arm, the costs of providing the intervention (including set-up, training, and ongoing support and supervision) will be calculated. Given the sample size, we would not conduct a full economic evaluation at this stage, as a much larger RCT is needed to undertake a cost-effectiveness analysis.

**Suicidality:** If during the recruitment, assessments or intervention delivery, the participant expresses thoughts, feelings or other or signs that indicate threat to his or her life, appropriate action will be taken to handle it. SoPs for dealing with low, medium and high risk would be as follows:

***Low risk:*** The patients with Low risk will be recommended for Tele follow up (IVRS- Interactive voice response system) and will be linked with the concerned unit for needed intervention

***Medium and High risk:*** The patient with medium and high risk will be advised to get admitted in emergency. If the patient permits/consents family members will be informed

about the patients heightened risk, information on monitoring and treatment.

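### The carer item is asked only at baseline, before the IMPACT 4S sessions it asks about, and Section 5.15 and Table 1 disagree on whether adherence is measured at six months

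*Protocol*

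**What the plan says.** **Carer item.** Section 5.15 heads the item "Carers/ family members involvement (at baseline") and words it in the past tense: participants report "whether they had been accompanied by a carer or family member at any of the intervention session", and whether a carer or relative helped them with intervention activities. Table 1 agrees with the heading. Its row reads "Carers/ family members’ involvement | X", and the one-, three- and six-month columns are empty.

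**Adherence.** Section 5.15 heads the measure "Smoking cessation pharmacotherapy adherence (one and three months"). It is a self-report over the last four days, computed as doses taken times 100 divided by doses prescribed. Values above 80% count as high and values below 80% as low. In Table 1 the row "Smoking cessation pharmacotherapy adherence" is marked at one, three and six months. Section 5.14 lists adherence as primary outcome 7.

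**Supply.** Section 5.1, Arm 2, gives three months as a minimum in one sentence. Later it says: "The medications will be provided for a period of three months in total". Anyone needing drug for longer is referred to the treating clinical unit.

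**The concern.** A question about what happened at sessions cannot be answered before the sessions take place. If the schedule is followed, Arm 2 participants answer at the one visit where they have little or nothing to report, and are not asked again. A pilot that wants to know how far carers take part in the intervention would then have no usable answer from this item.

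The adherence measure has a different problem. Two parts of the protocol give different visit schedules for a primary outcome. Section 5.16 tells researchers to collect follow-up data according to Table 1, so the six-month mark is likely to reach the data collection forms although the section defining the measure does not include that visit. The index needs doses prescribed in its denominator, and at six months some participants will have none.

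**Working it through.** The protocol states no figure to reproduce here. The check compares timings and adds simple date arithmetic.

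**Carer item**

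- Arm 2 size: 172 participants at 1:1 (Sections 5.18 and 5) gives 172 / 2 = 86.
- IMPACT 4S sessions: up to 15, spread over three to four months (Summary).
- Follow-up at one, three and six months comes after randomisation and baseline data collection (Section 5.16).
- Even if the first session fell on the baseline day, up to 15 − 1 = 14 sessions would follow it.
- Repeat of the item: none, in the text or in Table 1.

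Other places that might supply the information:

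| Source | Accompaniment | Help with activities |
| --- | --- | --- |
| Section 5.15 item, baseline only | asked too early | asked too early |
| Section 5.19, costing | yes | no |
| Section 6.3, three-month questionnaire | carers not named | carers not named |

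Brief advice is one contact on the enrolment day (Section 5.1, Arm 1), so a same-day answer is conceivable in Arm 1. The gap concerns Arm 2.

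**Adherence at six months**

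Inputs: a four-day recall, a follow-up visit at six months, and supply taken as exactly three months (one of the two readings of Section 5.1). The protocol gives no drug start date, so the start is an assumption and is varied. One month is taken as 30.44 days.

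- Visit day: 6 × 30.44 ≈ 183. The recall window is about days 179 to 183.
- Supply end = (start month + 3) × 30.44. Gap = start of window − supply end.

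| Assumed drug start | Supply ends (day) | Gap before window (days) |
| --- | --- | --- |
| Randomisation | 91 | 87 |
| Month 1 | 122 | 57 |
| Month 2 | 152 | 26 |
| Month 3 | 183 | none; window overlaps supply |

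For the first three starts, trial doses prescribed in the window are zero and the index is 0 × 100 / 0, which is undefined. It is defined only for people still prescribed drug, whether through the treating unit, a longer supply or a late start. The protocol gives no figure for how many that would be.

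**Cut-off**

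An index of exactly 80% arises whenever doses taken are four fifths of doses prescribed. The two classes are above 80% and below 80%, so this value belongs to neither.

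**The case against.** The strongest reply is that little is lost. Section 5.19 promises data on participants' travel, "including whether they were accompanied by carers/families, and the related travel and time costs". A reader might infer from the mistimed item that the intervention cost, secondary outcome 3, is compromised. It is not, because accompaniment is planned to be captured there. What remains uncovered is help with activities, which is not a listed primary or secondary outcome. This part of the reply stands.

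The second reply is that the section defining adherence limits it to one and three months, so the six-month mark may be a slip in the table. That is fair, and the defect is therefore a contradiction between text and table. A reader might go further and infer that six-month adherence would be empty for most participants, or would describe an unrepresentative remainder. The documents do not support this: the supply statements conflict, continuation by referral is allowed, and neither the start date nor the share continuing is given.

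The third reply concerns the measure itself. A reader might infer that four-day recalls sample too little of the treatment period and that the index should come from the log, since "An excel sheet log will be maintained for the dispensation, consumption, replenishing and monitoring of Bupropion/Nicotine gums". That does not follow. A short recall limits recall error, the protocol cites sources for it, and adherence is also noted in the counsellor's record book at each session. The log's completeness is not stated, it names gums but not patches, and the resupply process is described only for NIMHANS. Basing a primary outcome on the log would be a debatable redefinition and is not the correction of an error.

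**Conclusion.** Two scheduling points are wrong as written.

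First, the carer item is uninformative for Arm 2, about 86 participants. This rests only on the item's wording, its baseline-only timing in both text and table, and the session period given in the Summary.

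Second, Section 5.15 and Table 1 contradict each other on one of three visits for primary outcome 7. If the six-month visit is kept, the index is undefined for every participant with no drug prescribed in the recall window. How many that is cannot be derived from the protocol. The one- and three-month values are unaffected, so primary outcome 7 can still be reported.

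Two smaller points go with these: the conflicting statements on supply duration, which bear on when doses prescribed can be non-zero, and the unclassified value of exactly 80%.

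**What to change.** 1. In Section 5.15 and Table 1, move the carer and family item from baseline to follow-up visits after sessions have taken place, for example three months, with six months for any sessions held later. Participants already past baseline can be asked at those visits.
2. Make Section 5.15 and Table 1 agree on the visits for pharmacotherapy adherence. If six months is kept, report it as a separate descriptive item among those still prescribed drug, give that number, and keep it apart from the one- and three-month results.
3. Reconcile the two statements on supply duration in Section 5.1, Arm 2.
4. State to which adherence class a value of exactly 80% belongs.

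The cost is a few edits to Section 5.15, Section 5.1 and Table 1, matching changes to the forms, and a few questions moved to visits that are already planned. No added visit or change in sample size is needed.

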### Frequency and duration of follow-up

Following randomisation and baseline data collection, participants in each arm will be followed up at one, three and six months post-randomisation. At each follow-up visit, a trained researcher will administer a structured follow-up data collection form to the trial participant, obtaining information according to the follow-up schedule below (Table 1). The study flow diagram is given in Figure 1 below.

**Table 1. Baseline and follow-up measurement**

| **Measurement** | **Baseline** | **1 month**  **(Follow-up 1)** | **3 months**  **(Follow-up 2)** | **6 months**  **(Follow-up 3)** |
| --- | --- | --- | --- | --- |
| Demographic data | X |  |  |  |
| Preference for mode of intervention delivery | X |  |  |  |
| Carers/ family members’ involvement | X |  |  |  |
| Details of psychiatric medication | X | X | X | X |
| Smoking status | X | X | X | X |
| Nicotine dependence and urge to smoke | X | X | X | X |
| Quitting smoking intentions, motivations and behaviours | X | X | X | X |
| Mediators of smoking cessation | X |  | X | X |
| Health-related quality of life | X |  | X | X |
| Mental and physical health | X |  | X | X |
| Health services use | X |  | X | X |
| Physical body measurements (height; weight) | X |  | X | X |
| Smoking cessation pharmacotherapy adherence |  | X | X | X |
| Process evaluation questionnaire and interviews |  |  | X |  |

**Figure 1. Trial scheme diagram**

[figure not shown]

### Data collection and entry

Researchers in India and Pakistan will screen and recruit participants, and collect baseline and follow up information at one, three and six months. These researchers will receive three days training on trial procedures including taking informed consent, administering and completing the questionnaires and ethical issues such as autonomy of individual participants on making decisions about participation, freedom to withdraw from the trial without giving any reason or consequence, privacy, confidentiality, anonymity.

Data will be entered either in paper format or directly into an online survey tool (Qualtrics), ^46^ a secure and password protected resource available at the University of York. Collected data will be stored on a central database server.

All data will be stored and transferred following Health Insurance Portability and Accountability Act protocol. Any transfer of data from study sites to the University of York will be via the University of York’s secure and encrypted Drop-Off service. The staff involved in the trial will be trained on data protection processes. The staff will be strictly monitored to ensure compliance with privacy standards.

### Sample size and statistical analysis

#### Sample size

This will be an external feasibility trial and the main purpose is to explore the feasibility of the new intervention and the methods of recruitment, randomisation and follow up for a full trial. The sample size calculations are based on estimating participation and attrition rates and event rates of the primary outcome. If we identify 344 eligible subjects we will be able to estimate a participation rate of 50% to within a margin of error of ±5% and an attrition rate of 30% to within ±8%.^60^ Furthermore, an external feasibility study of at least 120 measured participants will provide robust estimates of event rates to inform the sample size calculation for the subsequent larger definitive fully powered trial.^61^ We will therefore aim to enrol 172 (86 per country) participants in the study in order to retain 120 for analysis assuming an attrition rate of 30%.

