#### Recruitment, Randomisation and Retention

1. What are the overall recruitment, enrolment and attrition rates?
2. What are the attrition rates per trial arm?

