#### Primary outcomes

1. Recruitment rates: Quantitative assessment of the acceptability of the research will be assessed by numbers screened, number eligible and those agreeing to participate.
2. Reasons for ineligibility/non-participation/non-consent of participants.
3. Length of time required to achieve the required sample size.
4. Retention in study: Assessed as a proportion of those enrolled in the study who are successfully followed-up at six months.
5. Retention in treatment: Evaluated by number of study intervention sessions attended as one measure of the feasibility and acceptability of the trial interventions to participants.
6. Intervention fidelity during the delivery of the behavioural support within the IMPACT 4S intervention, as well as for BA, assessed as one measure of feasibility of intervention delivery.
7. Smoking cessation pharmacotherapy adherence: For those in the IMPACT 4S arm, adherence to smoking cessation pharmacotherapy will be assessed as one measure of the feasibility and acceptability of the smoking cessation pharmacotherapies to participants.
8. Data completeness: Data will be checked for completeness as another measure of acceptability and feasibility of data collection methods, and to identify problem areas and solutions.

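### The ±8% margin for attrition does not match the 172 enrolled (about ±7 points), and it does not convey the wider margin per arm (about ±9.7 points)

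*Protocol*

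**What the plan says.** The sample size paragraph (Protocol section 5.18) starts from 344 eligible people. The claim made for that number is: "estimate a participation rate of 50% to within a margin of error of ±5% and an attrition rate of 30% to within ±8" per cent. The paragraph gives neither the confidence level nor the number of people behind either margin. It then sets the enrolment target: "We will therefore aim to enrol 172 (86 per country) participants in the study". The reason given is that 120 should be left to analyse if 30% are lost.

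Three other places bear on the denominator:

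- Section 5.14, primary outcome 4 (retention in the study): "Assessed as a proportion of those enrolled in the study who are successfully followed-up at six months".
- Section 2.3, under recruitment, randomisation and retention, asks for attrition overall and then separately: "What are the attrition rates per trial arm".
- Section 5 and section 5.10 fix allocation at 1:1, so 172 enrolled means 86 per arm.

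**The concern.** A loss rate is counted among everyone who could have been lost. Since retention is defined on those enrolled, attrition has the same denominator, 172 at the planned size. The ±8% is wider than 172 people would give and about what 120 people would give. 120 is the number expected to be left after attrition, and it cannot be the base for attrition itself.

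Retention is a primary outcome of this feasibility trial, and its precision is one of the stated grounds for the sample size. The one margin given fits neither attrition question in section 2.3: it is too wide for the overall rate and too narrow for the rate in each arm. A team planning the definitive trial might carry ±8% over to the arm-level rates and think them better known than they will be.

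**Working it through.** **Inputs.** 344 eligible, 50% participation, 30% attrition, 172 enrolled and 120 retained (section 5.18); denominator is those enrolled (section 5.14); 1:1 allocation, so 172/2 = 86 per arm (sections 5 and 5.10). Confidence level: not stated, taken as two-sided 95% and tested below.

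**Formula.** Wald half-width = z × √(p(1 − p)/n), with z = 1.96. For attrition p(1 − p) = 0.3 × 0.7 = 0.21. Retention of 70% gives the same product, so the margin is the same either way.

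**Step 1. Reproduce the plan's figures.**

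- Enrolment: 344 × 0.5 = 172; 120/0.7 = 171.4, rounded up to 172. Both agree with the plan.
- Participation: 1.96 × √(0.25/344) = 5.3 points, which rounds to the stated ±5%.
- Attrition of ±8%: solving for n gives 1.96² × 0.21/0.08² = 126. Any n from 112 to 143 gives a half-width that rounds to 8 (1.96² × 0.21/0.085² = 111.7; 1.96² × 0.21/0.075² = 143.4). Of the numbers in play (344, 172, 120, 86), only 120 lies in that range: 1.96 × √(0.21/120) = 8.2 points.

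**Step 2. Use the denominators that the protocol defines.**

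| Quantity | n | 95% half-width (Wald) |
| --- | --- | --- |
| Attrition 30%, overall | 172 | 1.96 × √(0.21/172) = 6.8 points |
| Attrition 30%, per arm | 86 | 1.96 × √(0.21/86) = 9.7 points |

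**Step 3. Does another interval method give ±8% on 172?**

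- Wald with continuity correction: ±7.1
- Wilson: ±6.8
- Exact (Clopper-Pearson, 52/172): −6.8/+7.5
- Worst case, p = 0.5: ±7.5 (7.47 before rounding)

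None rounds to 8 (the exact upper side is 7.45 before rounding). Per arm on 86, Wilson gives ±9.5 and the exact interval −9.4/+10.9.

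**Step 4. Does another confidence level give it?** The levels at which the participation margin rounds to 5% run from about 90.5% to 95.9%. On 172 they give attrition margins of ±5.8 to ±7.1 points. To reach ±8 on 172, z must be 0.08/√(0.21/172) = 2.29 (about 97.8% confidence). Participation would then be 2.29 × √(0.25/344) = 6.2 points, not 5. A 90% interval on 86 gives ±8.1, but participation at 90% would be ±4.4. No single level makes both stated margins fit with either of these attrition denominators.

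**The case against.** The strongest reply is that the plan promises attrition to within ±8% and will deliver better, so nothing promised is missed. The upper side of the exact interval is 7.5 points, so 8 is the smallest whole number that covers it. The first part stands: the overall figure is conservative. The second would require margins to be rounded up, and the companion figure is not: 5.3 is written as 5.

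Four stronger readings are tempting, and the documents do not support them.

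- *That the protocol demonstrably computed the margin on 120.* Section 5.18 shows no calculation and cites a source not available here. That ±8% does not fit 172 is arithmetic; that 120 was used is an inference, though the likeliest one.
- *That the participation margin is also wrong.* 5.3 against 5 is rounding to a whole number.
- *That the protocol misstates the per-arm margin.* It never presents ±8% as a per-arm figure. The gap is a missing precision statement for a question that it poses, not a second arithmetic error.
- *That the sample size loses its justification.* Section 5.18 has a separate basis, a minimum of 120 measured participants to estimate event rates. The 172 follows from that number and the 30% attrition assumption, and the ±8% plays no part in that step.

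A reader may also stumble on the paragraph's reference to event rates for the primary outcome, since abstinence is a secondary outcome here. The paragraph goes on to speak of the later definitive trial, whose primary outcome may be what is meant. That calls for a clarifying word at most.

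**Conclusion.** The stated attrition margin does not match the protocol's own denominator. For 30% attrition among 172 enrolled the margin is ±6.8 points (Wald), about ±7 by other methods, against the ±8 stated. For the attrition per arm that section 2.3 asks about, it is about ±9.7 points on 86, which the single figure does not convey.

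This rests on 95% confidence, which the protocol does not state but which reproduces its ±5%, and on the planned values of 172 enrolled and 30% attrition. The severity is minor: the overall figure errs on the cautious side, and enrolment, design and analysis are untouched.

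**What to change.** Amend the sample size paragraph in section 5.18 as follows:

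1. State the confidence level and the n behind each margin (344 eligible for participation, 172 enrolled for attrition).
2. Replace ±8% with about ±7% (±6.8%, n = 172) for overall attrition.
3. Add about ±9.7% (n = 86) for attrition per arm.
4. Optionally, say which trial's primary outcome the event rates refer to.

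The participation margin can stay at ±5% as a rounded figure. No margin for abstinence should be added on this account, since the protocol gives no assumed abstinence rate. The cost is a few words in one paragraph, with no change in participants, procedures or enrolment target.
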